#### Study Setting

This study is an open-label, single-center, prospective, observational study at one center in China.

#### Observation and Data Recording

Demographic data describing age, sex, main diagnosis, and past medical history are available at the inception of the study. Data related to the CPB time and application of antibiotics post-operation are available on the MUL-GM-CSCPB study Data Recording Sheet (Supplementary Table). The following observational data will be measured and recorded when patients are admitted to the ICU and at every sampling time.

Sequential (sepsis-related) organ failure assessment includes blood pressure; mean arterial pressure (MAP); and vasoactive drugs, including noradrenaline (NE), epinephrine (E), and dopamine (Dopa); PaO_2_/FIO_2_; Glasgow Coma Scale score; creatinine or urine output; bilirubin; and platelet count.Infection-related items include body temperature, WBC count, neutrophils, PCT, and antibiotics.Whether to be diagnosed with sepsis (according to Sepsis 3.0).Infection site and pathogenic microorganism.Nutrition and gastrointestinal function assessment including enteral or parenteral nutrition, bowel dilatation tested by ultrasound, gastric residual volume and intra-abdominal pressure measured via bladder.

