## Introduction

Complications after cardiac surgery are important factors that increase postoperative mortality after surgery (1). A prospective cohort study involving 4,446 consecutive patients undergoing cardiac surgery showed that there are some critical postoperative complications after cardiac surgery, including infection, renal failure, pulmonary complications, gastrointestinal complications, and multiorgan failure (2). The results showed that the in-hospital mortality was 3%, the postoperative renal failure incidence was 10%, the pulmonary complication rate was 32%, the gastrointestinal complication rate was 8%, the neurological complication rate was 7%, and the multiorgan failure rate was 2%. After undergoing cardiac surgery, patients are usually critically ill and require intensive care. Interestingly, we know from experience that some patients develop fever and hemodynamic instability after cardiac surgery without definitive etiological evidence. Previous studies have shown that systemic inflammatory response syndrome and postoperative fever are complications that develop after cardiac surgery (3, 4). We speculate that fever of unknown origin (FUO) and hemodynamic instability are related to systemic inflammatory response syndrome or sepsis. However, they may not be. The use of CPB or extracorporeal life support (ECLS) to support a patient during an intraoperative thoracic surgery is common, and cardiopulmonary bypass (CPB) is one of the risk factors for infection in patients undergoing cardiac surgery (5). On the one hand, it is reported that most of the early bloodstream infections of patients undergoing CPB are caused by gram-negative bacteria, which are commonly present in the intestinal flora (6). This finding indicates a relationship between the intestinal flora and infection or sepsis. On the other hand, the CPB process and duration of CPB determine the severity of organ ischemic injury. Intestines, as an ischemia-sensitive organ, will allow translocation of bacteria and endotoxins to the bloodstream (7). Therefore, the intestines play a role in postoperative sepsis or infection.

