## Method and Analysis

### Study Design

This protocol is designed as a prospective observational case–control study in patients who underwent cardiopulmonary bypass (CPB) due to cardiac surgery. Thirty healthy persons aged between 18 and 85, without digestive system disease, will be selected as the control group. The case group will include patients admitted to the intensive care unit (ICU) after cardiac surgery with CPB, which is performed by the Department of Cardiac Surgery of Peking Union Medical College Hospital. The patients enrolled should be divided into two groups according to their outcomes: one group of non-sepsis patients and the other group of sepsis patients after cardiac surgery. Sample collection will be terminated when each group receives 30 cases. These 60 cases will be regarded as the case group. Additionally, all the patients we observe will be further divided into survivors and non-survivors based on 28-days survival. Feces and blood samples will be obtained at certain time points (Figure 1).

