#### Metabolomics Analysis

The blood and stool samples will be analyzed using untargeted metabolomics. The analysis will be performed on an ultra-high-performance liquid chromatography system. To detect as many metabolites as possible, we plan to perform both polar ionic and lipid modes depending on the properties of the serum metabolites. The raw data will be converted into mzXML format and then processed by XCMS (20) software for peak picking and alignment. Metabolite features generated from XCMS will be further quantified by metaX software (21), including missing value imputation, data filtering, normalization, and comparison. Significant metabolites will be calculated using univariate (T/Wilcoxon test) and multivariate (PCA and PLS-DA) analyses integrated in metaX. The online HMDB database (22) and KEGG database (19) will be used to annotate the polar ionic metabolites by matching the exact molecular mass. The MS/MS spectrum from HMDB, MassBank (23) and an in-house database will assist in metabolite identification. For lipid identification, a LipidBlast database (24) will be used by matching the MS/MS spectrum and retention time. MetaboAnalyst (25) will be used for the identification of metabolic pathways.

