### Multi-Omic Data Analysis Plan

The data will be analyzed according to the case and control groups, sepsis and non-sepsis groups, and survivor and non-survivor groups, or some other classifications based on the pathophysiology.

Metagenomic and metabolomics statistical analysis will be performed using commercial software. To account for dependencies in repeatedly measured observations within a subject, a linear mixed-effect model will be used to assess the differences between the case group and the control group. Statistical analysis will be performed using SPSS (version 22, SPSS, Chicago, IL). A two-sided significance level of 0.05 will be used for statistical inferences. Combining principal component analysis (PCA), partial least squares discriminant analysis (PLS-DA), and orthogonal partial least square discriminant analysis (OPLS-DA), different metabolite profiles will be identified.

Receiver operating characteristic (ROC) analysis will be conducted to evaluate the utility of the potential biomarkers selected. Multivariate logistic regression analysis will be used to show the correlation between each factor and prognosis and changes in intestinal flora. A *p* < 0.05 will be considered statistically significant.

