## Discussion

This study is a prospective observational case–control study to analyze the variation in the intestinal microflora and metabolites in patients undergoing cardiac surgery with CPB and to observe the outcomes of patients with routine clinical interventions. Sixty patients will be enrolled to observe their outcomes (sepsis or non-sepsis) and their survival outcomes (28-days survival or death). Another 30 healthy people will be enrolled as the control group. We intend to collect blood and feces from these persons and to perform genomic and metabolome tests on pre- and post-surgery samples or control samples. According to bioinformatics analysis combined with mathematical modeling methods and statistical analysis, the relationship between intestinal microecological changes and sepsis will be determined.

We believe that FUO with hemodynamic instability after surgery is commonly seen and is likely to be a manifestation of the inflammatory response with sepsis. However, accurate diagnosis is quite difficult due to the low rate of detection of etiology. Infectious complications, especially sepsis or septic shock after cardiopulmonary bypass (CPB), are known to be a critical issue associated with severe morbidity and mortality (26). We know that intestinal ischemia-reperfusion occurring during cardiac surgery with cardiopulmonary bypass (CPB) will induce a systemic inflammatory reaction. Prolonged CPB could increase intestinal permeability and thus lead to endotoxin or bacterial translocation from the intestine to the bloodstream (27). Researchers determined intestinal fatty acid-binding protein (I-FABP), tumor necrosis factor alpha (TNF-alpha), interleukin 6 (IL-6), interleukin 8 (IL-8), and endotoxin levels in arterial blood at different times of CPB to indicate that the release of biomarkers that indicate ischemia-reperfusion damage to the gastrointestinal mucosa and endotoxemia may identify intestinal damage and bacterial translocation.

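### Sepsis vs non-sepsis: the only feature-level test stated, t/Wilcoxon for metabolites, takes no covariate, although CPB time and the pre-operative value are collected and CPB time may confound the comparison

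*Protocol article*

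**What the plan says.** **Test.** Metabolomics Analysis states: "Significant metabolites will be calculated using univariate (T/Wilcoxon test) and multivariate (PCA and PLS-DA) analyses integrated in metaX". Multi-Omic Data Analysis Plan adds OPLS-DA and sets the level: "A two-sided significance level of 0.05 will be used for statistical inferences".

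**Contrasts.** The same section says: "The data will be analyzed according to the case and control groups, sepsis and non-sepsis groups, and survivor and non-survivor groups". It assigns the linear mixed-effect model to case vs control. It also plans a multivariable logistic regression relating factors to prognosis and to changes in the flora, but does not list the factors.

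**Group sizes.** Study Design: "Sample collection will be terminated when each group receives 30 cases. These 60 cases will be regarded as the case group", that is, 30 sepsis and 30 non-sepsis patients.

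**CPB time.** Observation and Data Recording lists "Data related to the CPB time and application of antibiotics post-operation" among the recorded items. The Introduction says of the bypass process that it and the "duration of CPB determine the severity of organ ischemic injury", and calls the intestine sensitive to ischemia. The Discussion says "Prolonged CPB could increase intestinal permeability" and so lead to passage of endotoxin or bacteria into the blood. It then names translocation as a suspected route to infection and sepsis.

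**Samples.** Under Sample Collection, each patient gives feces and blood the day before surgery (T1) and within 24-72 h of ICU admission (T2).

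**The concern.** Sepsis vs non-sepsis is the contrast closest to the study's question. The article states a feature-level test that can be applied to it, and that test cannot take a covariate.

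CPB time is settled in theatre, before the T2 sample is drawn, so it cannot be a consequence of a T2 feature. If longer bypass shifts a metabolite and also raises sepsis risk by some route other than that metabolite, the metabolite will differ between the groups without any link of its own to sepsis. A marker of operation length could then pass as a sepsis marker and go forward to the planned ROC analysis.

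The T1 value matters for a related reason. The hypothesis concerns change after surgery. A comparison of T2 values alone mixes change with differences that existed before the operation, and it gives up the precision that T1 offers.

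**Working it through.** **Nothing to reproduce.** The article gives 30 vs 30 with no effect size, SD or power. For scale, 80% power at two-sided 0.05 needs a difference of (1.960 + 0.842) × √(2/30) = 0.72 SD.

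**Inputs from the article.** 30 per group; two-sided 0.05; t/Wilcoxon test.

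**Assumed inputs, not in the documents.** CPB-time gap between sepsis and non-sepsis, 0.3-0.8 SD. Within-group correlation r of CPB time with the feature, 0.2-0.5. T1-T2 correlation ρ, 0.3-0.7.

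**Step 1: bias from CPB time.** For a feature with no sepsis effect of its own, the spurious difference is r × gap, in SD units. This runs from 0.2 × 0.3 = 0.06 to 0.5 × 0.8 = 0.40.

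**Step 2: false-positive rate.** 20,000 simulated data sets per row, tested by t, by Wilcoxon, and by a linear model with CPB time as covariate:

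| Gap (SD) | r | Bias (SD) | t | Wilcoxon | Adjusted |
|---|---|---|---|---|---|
| 0.3 | 0.2 | 0.06 | 0.055 | 0.054 | 0.049 |
| 0.3 | 0.3 | 0.09 | 0.063 | 0.060 | 0.051 |
| 0.3 | 0.5 | 0.15 | 0.090 | 0.085 | 0.050 |
| 0.5 | 0.2 | 0.10 | 0.070 | 0.065 | 0.051 |
| 0.5 | 0.3 | 0.15 | 0.087 | 0.084 | 0.046 |
| 0.5 | 0.5 | 0.25 | 0.157 | 0.146 | 0.053 |
| 0.8 | 0.2 | 0.16 | 0.093 | 0.088 | 0.050 |
| 0.8 | 0.3 | 0.24 | 0.146 | 0.137 | 0.051 |
| 0.8 | 0.5 | 0.40 | 0.330 | 0.309 | 0.046 |

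Simulation error near 0.05 is √(0.05 × 0.95 / 20,000) = 0.0015, so the adjusted column is close to nominal throughout. The noncentral t distribution agrees for the mid case: a bias of 0.15 SD gives 0.088.

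**Step 3: T1 and power.** With T1 as covariate the residual SD is √(1 − ρ²). By normal approximation, power = Φ(0.5 / (SD × √(2/30)) − 1.960) for a 0.5 SD effect:

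| ρ | Residual SD | Power |
|---|---|---|
| unadjusted | 1.000 | 0.491 |
| 0.3 | 0.954 | 0.528 |
| 0.5 | 0.866 | 0.609 |
| 0.7 | 0.714 | 0.774 |

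**Step 4: T1 and bias.** If the groups already differ by 0.3-0.5 SD at T1 (assumed), the unadjusted T2 comparison carries a bias of ρ × imbalance. That is 0.3 × 0.3 = 0.09 to 0.7 × 0.5 = 0.35 SD. The false-positive rate is then 0.064 to 0.273.

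**The case against.** The strongest reply is that the article does plan a multivariable model. The logistic regression may well include CPB time, and an article can leave its covariate list to an analysis plan that is not shown. This stands, and it rules out saying that the study has no adjusted analysis. It does not answer the point. The regression is not tied to the metabolite tests, and the article positively states the test by which metabolites are declared significant.

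Three stronger readings are tempting, and the text does not support them.

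- *That flora will be tested unadjusted.* The t/Wilcoxon sentence concerns metabolites. The article names no group test for taxa in this contrast.
- *That the protocol names CPB duration as a cause of infection.* The Introduction calls CPB itself a risk factor for infection, and every case had CPB. The link from duration to sepsis has to be assembled from ischemic injury, permeability and translocation.
- *That T1 is unused.* The article speaks of analysing changes in the flora, which presumably draws on T1. What can be said is that T1 has no stated role in this contrast.

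It can also be said that the article's only route from duration to sepsis runs through the gut. If a given feature were the sole step on that route, CPB time would not confound it. That is fair, and it is why the claim is that CPB time may confound. An untargeted screen tests many features, and most cannot be that sole step.

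Finally, unadjusted screening of candidate markers is common practice. That is a reason to keep the unadjusted tests, but not to report them alone.

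**Conclusion.** The point holds as an improvement to a stated method. For sepsis vs non-sepsis, the one feature-level test that the article states takes no covariate. CPB time, which by the article's own reasoning may act on both sides of the comparison, is recorded, and a T1 sample is taken.

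The size rests wholly on assumed values. Over the ranges used, the false-positive rate per feature is about 5.5-33% unadjusted and about 5% adjusted. The low end is close to nominal; the mid case (gap 0.5 SD, r = 0.3) is about 9%. The gain in power from T1, from about 0.49 to 0.53-0.77 for a 0.5 SD effect, depends on an assumed T1-T2 correlation of 0.3-0.7.

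A reader might infer that the sepsis findings will be spurious, or that adjustment for CPB time would make them causal. Neither follows. The documents do not show that CPB time differs between the groups, and other confounding, such as by antibiotics, would remain.

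**What to change.** For sepsis vs non-sepsis, state that each suitably transformed T2 feature will be modelled linearly on sepsis group, the T1 value of the same feature, and CPB minutes. Apply this to metabolites and likewise to taxa. Report the unadjusted t/Wilcoxon results alongside, so that readers can see which features depend on the adjustment. List the factors of the logistic regression and include CPB time among them. Say in the report that adjustment for these two covariates does not remove other confounding, antibiotics included.

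The cost is about two degrees of freedom among 60 patients (residual 58 falls to 56). No new data are needed, since the article already plans to record CPB time and to take a T1 sample from each patient.

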#### Grouping by Outcomes

The primary outcome is patients with cardiovascular surgery with CPB and healthy people.

The secondary outcomes are as follows.

After sample collection, the case group will be selected and divided into two groups according to their clinical outcomes.

Sepsis group (sub grouped by suspected or documented infection) and non-sepsis group;Survivors and non-survivors based on the 28-days survival.

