There is growing evidence that microbiomes play an indispensable role in human health and disease. Meanwhile, a lot of progress has also been made in association studies between disease and intestinal metabolites. As early as the later part of the nineteenth century, researchers found that peritonitis could result from the passage of bacteria from organs adjacent to the peritoneal cavity. The “gut origin of sepsis” became a theory of interest to clinicians (8). The theory of intestinal flora translocation has gradually emerged. Dickson et al. found the lung bacteria of patients with ARDS, which is correlated with systemic inflammation translocated from the intestine (9). Singer et al.'s research in mice and patients who died of sepsis suggests that bacterial translocation could be associated with sepsis in acute neuroinflammation (10). Other studies found that a ratio of Bacteroidetes to Firmicutes (B/F ratio) of >10 or <0.10 in the gut microbiota may suggest a high risk of death (11). We hypothesized that, except for iatrogenic infections, endogenous bacterial translocation after CPB is a possible mechanism of early sepsis or septic shock in these patients. The use of intestinal microecological studies and metabolite studies can help determine whether changes in the intestinal flora and metabolites after cardiac surgery with CPB are associated with sepsis. This research method has become very mature in clinical research. There are a series of studies on the host microbiota with neurologic, metabolic, cardiovascular, or gastrointestinal disorders (12–16). Studies on the association between disease and intestinal metabolites have also made essential progress. We hypothesize that sufficient information related to the pathogenesis of sepsis can be obtained from studies on intestinal microecology and metabolites.

This study will identify the variation in the gut microbiota and host metabolite profiles of patients after undergoing cardiac surgery with CPB. The changes in the intestinal flora in patients with sepsis and patients with worse outcomes will be analyzed emphatically. Combined with clinical data, the possible pathogenesis of FUO and patients with hemodynamic instability and their association with infection will be analyzed. This study may also indicate whether the phenomena of FUO and hemodynamic instability are attributed to sepsis or a purely inflammatory response.

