#### Definition

The clinical criteria according to the third international consensus (Sepsis-3) (17):

Sepsis: suspected or documented infection and an acute increase of ≥2 SOFA points.

Suspected infection group will be identified as those who had body fluids sampled for culture and received antibiotics but had a negative culture result.

The documented infection group will be identified as those who had body fluids sampled for culture with a positive result.

Survivors: Patients that survive for 28 days or more after surgery.

Non-survivors: Patients that survive <28 days after surgery.

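### The sepsis versus non-sepsis contrast varies infection and organ dysfunction together, so on its own it cannot support the aim of telling sepsis from pure inflammation

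*Protocol article*

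**What the plan says.** - **Sepsis.** The section Definition follows Sepsis-3: "Sepsis: suspected or documented infection and an acute increase of ≥2 SOFA points". Suspected infection means culture taken, antibiotics given and culture negative; documented infection means a positive culture.
- **Comparator.** Study Design splits enrolled patients into "one group of non-sepsis patients and the other group of sepsis patients after cardiac surgery", and Grouping by Outcomes repeats the split: "Sepsis group (sub grouped by suspected or documented infection) and non-sepsis group". The non-sepsis group has no definition of its own, no SOFA condition and no matching on severity.
- **Size.** "Sample collection will be terminated when each group receives 30 cases" (Study Design).
- **Aim.** The Introduction asks whether flora and metabolite changes are associated with sepsis. It adds that the study may show whether unexplained fever and haemodynamic instability are "attributed to sepsis or a purely inflammatory response".
- **Analysis.** The Multi-Omic Data Analysis Plan names case/control, sepsis/non-sepsis and survivor/non-survivor comparisons, plus unspecified other classifications. It uses a two-sided 0.05 level, ROC analysis of selected markers and a logistic regression whose factors are not named.
- **Data.** Observation and Data Recording lists the SOFA components, antibiotics, infection site and pathogen, recorded at ICU admission and at each sampling.

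**The concern.** Every septic patient has the SOFA rise by definition. The non-sepsis group is the complement, so it may mix three kinds of patient: neither infection nor SOFA rise, infection without SOFA rise, and SOFA rise without infection. Unless all of them have the rise, the two groups differ in infection and in organ dysfunction at once.

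The subgrouping into suspected and documented infection does not help. It divides only the septic side, where everyone already has the rise. Counting only culture-positive cases would likewise leave the comparator without a SOFA condition.

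At stake is the interpretation. The Discussion says that intestinal ischaemia-reperfusion during surgery with bypass "will induce a systemic inflammatory reaction", so the protocol itself names a route to inflammation other than infection. A taxon or metabolite that follows organ dysfunction can then be significant, and give a respectable AUC, without any link to infection. Reading it as evidence for sepsis over inflammation would go beyond what the contrast can show.

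**Working it through.** The protocol gives no effect size, SD or power for this contrast, so there is no figure of its own to reproduce. The check is an illustration.

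**Inputs from the protocol:** 30 v 30; two-sided 0.05; all septic patients have a SOFA rise of at least 2.

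**Assumed, because the protocol gives neither:**
- *d*: shift, in SD, of a marker in anyone with the SOFA rise. The marker has no infection effect. Range 0.8 to 1.0.
- *q*: share of non-septic patients who also have the rise. Range 20% to 80%.

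**Step 1: discrimination.** The septic group is shifted by *d*, and a fraction *q* of the comparators is shifted too. The mean difference is (1 − q)·d, and

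AUC = 0.5q + (1 − q)·Φ(d/√2).

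Here Φ(0.8/√2) = 0.714 and Φ(1/√2) = 0.760. For d = 1 and q = 0.2: 0.10 + 0.8 × 0.760 = 0.71. For d = 1 and q = 0.8: 0.40 + 0.2 × 0.760 = 0.55.

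**Step 2: chance of p<0.05.** Simulated two-sided Mann-Whitney tests, 30 v 30. Repeat runs agree within about 3 percentage points.

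| q | d = 0.8: AUC | d = 0.8: p<0.05 | d = 1.0: AUC | d = 1.0: p<0.05 |
|---|---|---|---|---|
| 20% | 0.67 | 65% | 0.71 | 82% |
| 40% | 0.63 | 41% | 0.66 | 57% |
| 60% | 0.59 | 21% | 0.60 | 28% |
| 80% | 0.54 | about 8–10% | 0.55 | about 8–10% |
| 100% | 0.50 | about 5% | 0.50 | about 5% |

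**Step 3: does restricting the comparator remove the effect?** The last row says yes, but only because the model treats dysfunction as a yes/no switch. Suppose instead that the marker rises by 0.15 or 0.25 SD per SOFA point, and that rises are 2 + Poisson(3) in septic patients against 2 + Poisson(1) in uninfected comparators (all assumed). With 30 v 18, the restricted contrast is still significant in roughly 13–15% and 30–33% of trials. Restriction therefore has to be combined with adjustment for the size of the rise.

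**Step 4: precision.** Power to detect a true 0.8 SD infection effect, 30 septic patients against *n* comparators, before any SOFA adjustment:

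| n | 30 | 18 | 12 | 6 |
|---|---|---|---|---|
| Power | about 83% | 74% | 59% | 38% |

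**The case against.** The strongest reply is that organ dysfunction is part of sepsis under the definition adopted, so sepsis versus non-sepsis answers the stated question of association with sepsis. This stands. A reader might infer that the contrast or the Sepsis-3 definition is wrong; the documents do not support that. The grouping is also listed among the secondary outcomes, and the sentence on sepsis versus pure inflammation is hedged. But that aim is stated, and no named comparison serves it.

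A second reply is that covariates and further contrasts belong in a fuller document, and that other classifications are left open. In part this is fair: nothing excludes the missing comparison. But the article does fix the groups, definitions and contrasts, and these do not separate the two explanations.

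A reader might also infer that the protocol expects organ dysfunction without infection, since the Introduction cites 32% pulmonary complications and 10% renal failure. Those are overall rates in a cohort where infection is also listed as a complication. They are not SOFA rises and are not said to be uninfected. Nor does the Discussion say that ischaemia-reperfusion acts alone.

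Finally, all comparators are ICU patients after bypass, and the Introduction calls such patients usually critically ill, so the share with a SOFA rise could be high and the problem small. This stands too: the size cannot be settled from the documents.

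**Conclusion.** The point holds as a limit on interpretation. The contrast supports statements about sepsis as a syndrome. By itself it does not support statements that a marker reflects infection rather than organ dysfunction or inflammation, and so it cannot deliver the sepsis-or-inflammation aim in the Introduction.

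The structural part follows from the definitions alone. The size rests on two assumptions, the marker shift and the share of non-septic patients with a SOFA rise. Across the range examined, the rate for a marker of dysfunction only runs from near 80% down to 8–10%. It would be wrong to infer that any marker of organ dysfunction will pass as a sepsis marker, or that a restricted comparator cures the problem outright.

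A change is worthwhile because it is cheap and most of the data are already collected.

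**What to change.** 1. Keep the sepsis versus non-sepsis contrast, and state that its markers reflect infection and organ dysfunction together.
2. In Grouping by Outcomes and the Multi-Omic Data Analysis Plan, add one named supportive contrast: septic patients versus patients with no suspected or documented infection and a SOFA rise of at least 2. Measure the rise from the same reference score in both groups, and adjust for the size of the SOFA change.
3. Report that contrast as an estimate with its interval and the number of comparators. Claim infection-specificity only where this estimate supports it.
4. Do not make significance in it a pass/fail gate. For a true 0.8 SD effect, the chance of being significant in both contrasts is only about 69%, 58% and 36% with 18, 12 and 6 comparators.

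**Cost.** No new patients or samples. The comparators may be few, particularly because culture-negative patients given antibiotics count as suspected infection, so precision will be low (Step 4), and SOFA adjustment may lower it further. Identifying uninfected patients also requires knowing whether a culture was taken. The article's list of recorded items gives infection site and pathogen but not that fact, so check that the data recording sheet captures it.
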